### Secondary outcomes

This trial will also assess several secondary outcomes including the total number of neonates identified with the m.1555A>G genetic variant (positive result) as a proportion of the study population. An assessment of resource impact will be undertaken, including a health economic analysis of additional staff time to secure sample and testing and costs associated with alternative antibiotic prescribing for any positive tests. We will record the number of neonates where testing was not undertaken and the rationale for this. Correlation of the POCT result with the current in-house reference assay will be assessed and any test fails will be reported. In the acute neonatal setting, delivering antibiotics in a timely manner is critical and this should ideally be within an hour after admission. As such, we will assess whether the time to antibiotic administration after admission is impacted by implementation of the genetic POCT. A reference time to antibiotic was measured over a month-long period before implementation.

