**Figure 1 F1:**
[figure not shown]
Flow diagram demonstrating the admission, testing and prescribing process in the Pharmacogenetics to Avoid Loss of Hearing trial. The time that a decision was made to prescribe antibiotics represents time 0. If antibiotics were not prescribed, then time 0 is represented by the time of admission. POCT, point of care test.

As part of the study the following variables will be recorded; participant demographics, admission time, time of decision to prescribe, time swab taken, time assay started, time of assay result, assay result, time of antibiotic prescription, antibiotics prescribed. Where a positive result is identified and antibiotic therapy is required, an alternative antibiotic regimen (standard non-gentamicin pathway as per hospital guidelines) will be prescribed and a referral should be made to clinical genetics for familial cascade testing. Where there is a test-fail, standard of care should be followed, that is, the baby should be administered gentamicin if clinically indicated. Negative results will not be formally reported to the parents. However, all parents will be provided with information on the study in their information pack, allowing them to contact the study team for further information if they wish.

Assay performance will be assessed throughout the study, with at least 10% of samples each month tested via gold-standard sequencing. Any positive samples will also be confirmed as per standard clinical pathways. Any divergence between the POCT and gold-standard methodology will be reviewed by the trial management committee.

Data collection will be undertaken contemporaneously by the clinical staff and any missing data will be collected by the NICU research nurses. Data will be entered into an electronic database by the clinical team and a study ID will be generated. The participants will subsequently be anonymised to the research team. If an individual is not tested for any reason (eg, test overlooked, staff availability or the individual meets the exclusion criteria), these incidences will be captured retrospectively by NICU research nurses by checking daily admission records and the reasons will be documented.

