### Samples size

The sample size (approximately 900 babies) is estimated based on the expected number of admissions across both clinical sites over an approximate 10-month trial period. To achieve a statistical power of 90% with a 5% significance level, a margin of 0.5 (in Cohen’s d, which equates to about 7 min difference given the SD in the control sample) and a control sample of N=50, a test sample size of 112 is required. With the forecast test sample size of 900, statistical power should be around 95% to detect variance in clinical timings before and after implementation.

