### Statistical analysis

For the primary outcome, simple descriptive statistics will be used to provide a metric for the proportion of babies tested for the variant over the number who were ultimately prescribed aminoglycoside antibiotics.

Regarding the secondary outcome measures, the objective is to establish that the introduction of the POCT does not significantly impact the time between admission to NICU and the prescription of antibiotics for acute admissions. For the purposes of this analysis, those babies receiving antibiotics within the first 2 hours of admission, representing acute antibiotic administration, will be compared. The burden of proof rests on the research hypothesis, meaning the null hypothesis is that the new POCT does impact this quantity. This is a so-called non-inferiority significance test. The quantity of interest is the mean difference between the admission to ICU and prescription of antibiotics timestamps in two situations: with and without the POCT test 
$\left(\mu_{c},\mu_{t}\right)$
. The null hypothesis is that the difference between these quantities is greater than or equal to some prespecified margin 
(Δ)
 that is, 
$H_{0}:\mu_{c}-\mu_{t}\geq \Delta ;H_{A}:U_{t}-U_{c}<\Delta$
. A type I error here is concluding the time durations are equivalent when in fact the time to antibiotic with the POCT is greater.

The two samples are of unequal size, with the control (‘before implementation’) sample having about 
$n_{c}$
=50, and a forecasted test sample size of around 
$n_{t}$
=900. We also have no insight into population variance and cannot assume they are the same in both groups (it may eg, take some staff members longer to carry out the new test than others). As such, a one-sided Welch t-test will be used to reject or not reject the null hypothesis.

Throughout the study we anticipate that there will be iterative updates to the POCT technology, as avenues for optimisation emerge because of our findings from real-world implementation. The timings of these updates will be recorded and separate post-hoc statistical analysis will be undertaken to assess the impact of each update.

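### The timing comparison selects babies on the time it sets out to test (antibiotics within 2 hours), which tilts it towards non-inferiority by an amount that depends on how any delay is distributed

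*Protocol article*

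**What the plan says.** Under Secondary outcomes, the protocol article states that "we will assess whether the time to antibiotic administration after admission is impacted by implementation of the genetic POCT", using a reference time measured over one month before implementation. Under Statistical analysis it describes a slightly different quantity: "The quantity of interest is the mean difference between the admission to ICU and prescription of antibiotics timestamps in two situations", that is, with and without the POCT.

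The same section fixes the analysis set: "those babies receiving antibiotics within the first 2 hours of admission, representing acute antibiotic administration, will be compared". The only reason given is that this represents acute administration. The article describes no analysis without the cut and no before-and-after comparison of the proportion treated beyond 2 hours.

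The inference is described as follows: "This is a so-called non-inferiority significance test", and "a one-sided Welch t-test will be used to reject or not reject the null hypothesis". The sample size section sets the margin at 0.5 in Cohen's d, "which equates to about 7 min difference given the SD in the control sample".

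The variables recorded during the study include "participant demographics, admission time, time of decision to prescribe, time swab taken, time assay started, time of assay result". Time of decision to prescribe is therefore collected, and the testing process section makes it time 0 for babies who are prescribed antibiotics. It is not used to define the acute group.

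**The concern.** The 2-hour filter is applied to time from admission to receipt of antibiotics. That is the outcome named under Secondary outcomes. It is also an interval that contains the admission-to-prescription time named under Statistical analysis, since prescription precedes receipt. Either way, membership of the analysis set is settled after the POCT could have affected it.

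A cut applied equally to both periods does not cancel out. Babies treated late for unrelated reasons leave both groups. A baby held past 2 hours because of the POCT can only be in the implementation group, and that baby is dropped. The longest POCT-related times therefore go missing from one side only, and the mean difference shrinks.

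In a non-inferiority test this is the unsafe direction. The article itself names the type I error as concluding that times are equivalent when they are longer with the POCT. This comparison is the only hypothesis test the article describes, and it bears on the part of the primary objective about not disrupting standard care. A long delay confined to a minority of babies is the pattern it would be least able to see.

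**Working it through.** **Inputs from the protocol article**
- Margin: 0.5 SD, about 7 min, so control SD = 7 / 0.5 = 14 min.
- Control n = 50; required test n = 112; forecast test n = 900, which counts expected admissions and not babies treated within 2 hours.
- Significance level 5%, one-sided Welch test, cut at 120 min.
- Assay run time 26 min (Abstract); antibiotics ideally within 60 min of admission (Secondary outcomes).

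**The plan's own figures first.** With one-sided alpha 0.05, d = 0.5 and 50 controls, the noncentrality parameter is 0.5 / √(1/50 + 1/n_t). At n_t = 112 power is 0.900 (pooled t) or 0.899 (Welch). At n_t = 900 it is 0.960 (Welch), against the stated figure of around 95%. The sample size statement reproduces. It assumes that the analysed babies represent the delay, which is the matter at issue here.

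**Effect of the cut**

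Assumptions that are not in the documents: control times lognormal with mean 50, 60, 75 or 85 min and SD 14 min; 450 POCT babies analysed; POCT times follow the control distribution plus a delay. Non-inferiority is declared when

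(mean_t − mean_c − 7) / √(s_t²/n_t + s_c²/n_c) < −t(0.95, Welch df).

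The true mean delay was held at about 9 min, beyond the margin, and only its pattern was varied:
- 12% of babies delayed 75 min: 0.12 × 75 = 9.0 min
- 17.5% delayed 52 min (two assay runs): 0.175 × 52 = 9.1 min
- 35% delayed 26 min (one assay run): 0.35 × 26 = 9.1 min
- every baby delayed 9 min

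Percentage of simulated trials that wrongly declare non-inferiority:

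| Pattern of delay | Cut, mean 50 | Cut, mean 60 | Cut, mean 75 | Cut, mean 85 | All babies kept |
|---|---|---|---|---|---|
| 75 min in 12% | 52 | 90 | 96 | 97 | about 1 or less |
| 52 min in 17.5% | 2 | 8-10 | 69-70 | 94 | about 1 or less |
| 26 min in 35% | 0.5 | 0.7 | 2 | 12-13 | about 1 or less |
| 9 min in all | about 1 or less | about 1 or less | about 1 or less | about 1 (up to 1.6) | about 1 or less |

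Ranges within a cell reflect simulation error between repeat runs. In the first row at a control mean of 60 min, about 11% of POCT babies fall outside the cut and the observed mean difference drops from 9.0 to about 1.0 min.

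**Further scenarios with 900 POCT babies** (normal or lognormal times, control means 45 to 75 min, SD 14)
- 10% delayed 90 min (true difference 9 min): passed in 89-98% of runs with the cut, at most 1% without.
- A uniform 7-min delay, exactly at the margin: passed in about 4-6% either way, so there is almost no bias.
- A uniform 7-min delay with a wider spread of times (mean 60, SD 30; mean 75, SD 40): the observed difference shrinks to 6.1 or 5.5 min and the error rate is about 8-9%, against a nominal 5%.

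**The case against.** The strongest reply is that some cut is needed. All admissions are eligible, including transfers. Babies for whom the decision to treat came many hours or days later would swamp a 7-min margin if they entered a mean admission-to-antibiotic time. That stands as a reason to isolate acute admissions. It does not justify isolating them by the outcome. It also limits the all-babies column above, which contains no late-decision babies and keeps SD 14 without the cut.

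The second reply is that the large error rates come from a delay pattern that the documents do not report. This stands too. Waits of one assay run are nearly harmless unless control times already sit near 85 min, well beyond the one-hour ideal.

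A reader might infer more than the article supports:
- *That the control group loses nobody to the cut.* It does lose babies, because the cut applies in both periods. Controls lose none that the POCT delayed, which is a narrower statement.
- *That failed runs and repeat swabs will routinely push babies past 2 hours.* The article sends a failed test to standard care, describes no repeat swab, and says normal practice continues while the assay runs. Long delays remain possible, since the article expects some test failures and notes that some staff may take longer, but it does not show that they are common.
- *That the result will be wrong.* Nothing in the article shows that the POCT delayed anyone.

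Finally, this is a secondary outcome. The primary outcome is a descriptive proportion and is untouched.

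**Conclusion.** The concern holds as a matter of structure and direction. The analysis set is defined by the outcome, or by an interval containing it, after the POCT could have acted, and the resulting bias favours non-inferiority. That follows from the stated rule and needs no assumption about the data beyond the possibility that the POCT delays some babies past 2 hours.

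The size is uncertain. For a true mean delay of about 9 min against a 7-min margin, false non-inferiority ranges from about 1% or less (uniform delay), through about 0.5-13% (26 min in 35% of babies) and about 2-94% (52 min in 17.5%), to about 52-97% (75 min in 12%). These ranges rest on assumed control means of 50 to 85 min, SD 14 min and lognormal times. The cut is close to harmless for small shared delays and can conceal long delays concentrated in a few babies. The article gives no times from which to tell which case applies.

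**What to change.** 1. Define the acute set by a time fixed before the POCT can act: a recorded decision to prescribe within a stated window after admission. Keep every such baby, however late the antibiotic was given. Do this in both periods if control-month decision times exist or can be retrieved.
2. Whether or not step 1 is possible, report for each period the number and proportion of antibiotic-treated babies beyond 2 hours, and the proportion within 60 min.
3. Make the 2-hour subset a sensitivity analysis. If it must remain the main analysis, limit its conclusion to babies treated within 2 hours.
4. Use the same time, prescription or administration, for both the filter and the outcome.

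**Cost.** Recruitment has closed but the article says analysis is ongoing, so no new participants are needed. It is still more than a change of wording. The list of recorded variables describes the study period, and for the control month the article mentions only a reference time to antibiotic, so the records of about 50 controls may need checking. An uncut analysis restricted by indication is not a ready substitute, because no indication variable is listed. The SD will probably be larger and the result may be less favourable. Step 2 is cheap and would by itself show whether the cut matters.

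### The printed hypotheses of the non-inferiority timing test contradict each other: the null has the wrong sign, and a harmful delay lies in neither hypothesis

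*Protocol article*

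**What the plan says.** The timing comparison is a secondary outcome of the Protocol article. Its Statistical analysis section puts the burden of proof on showing no effect, so that "the null hypothesis is that the new POCT does impact this quantity", and calls the test non-inferiority.

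The two means are introduced as the interval between "timestamps in two situations: with and without the POCT test", followed by the pair (μc, μt). The section continues: "The null hypothesis is that the difference between these quantities is greater than or equal to some prespecified margin". The formula that spells this out is "H_{0}:\mu_{c}-\mu_{t}\geq \Delta ;H_{A}:U_{t}-U_{c}<\Delta", that is, H0: μc − μt ≥ Δ and HA: Ut − Uc < Δ.

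The error to be controlled is then put in words: "A type I error here is concluding the time durations are equivalent when in fact the time to antibiotic with the POCT is greater". The next paragraph fixes the subscripts through the sample sizes, "with the control (‘before implementation’) sample having about" nc = 50 "and a forecasted test sample size of around" nt = 900, and names the procedure: "a one-sided Welch t-test will be used to reject or not reject the null hypothesis".

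The sample-size section gives the level (5%), power (90%), margin (0.5 in Cohen's d, about 7 min), control sample (50) and required test sample (112). It puts power at around 95% with 900.

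**The concern.** A non-inferiority null has to contain the harm that the trial wants to rule out. Here the harm is a longer time to antibiotics with the POCT. With c as control, the printed null instead contains the case in which the POCT shortens the time by Δ or more. The subtraction runs c − t in H0 and t − c in HA, and the symbol changes from μ to U between them. The order in which the means are introduced (with, then without, against c, then t) labels them the opposite way from the sample sizes.

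The primary outcome is analysed descriptively, so this is the only hypothesis test that the article names. (Post-hoc analyses after device updates are also planned, without a named test.) It bears on the primary objective, which asks that the test be integrated without disrupting standard care. The article also says that it is the null that will be rejected or not rejected. A wrong sign in that line could therefore carry into the decision rule.

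**Working it through.** **1. Which outcomes each hypothesis covers.** Let δ be the mean time with the POCT minus the mean time before implementation, with Δ > 0.

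| Labelling | Printed H0 | Printed HA | In both | In neither |
|---|---|---|---|---|
| c = before, t = POCT (as in nc, nt) | δ ≤ −Δ | δ < Δ | δ ≤ −Δ | δ ≥ Δ |
| c = POCT, t = without (as in the with/without order) | δ ≥ Δ | δ > −Δ | δ ≥ Δ | δ ≤ −Δ |
| Required by the prose | δ ≥ Δ | δ < Δ | none | none |

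Under the first labelling HA is right and H0 is reversed. Under the second H0 is right and HA is reversed. In both cases every point of H0 also satisfies HA, so rejecting H0 does not establish HA. The second labelling also conflicts with nc being the pre-implementation sample.

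**2. The plan's own figures.** Inputs: one-sided 5%, true difference 0, d = 0.5, nc = 50. With nt = 112 the noncentrality is 0.5/√(1/50 + 1/112) = 2.94, and a pooled noncentral t on 160 df gives power 0.9001. This reproduces 112. The Welch version needs 115, and a two-sided 5% test would need 274 (pooled t), so the plan used a one-sided 5% test. With nt = 900, power is 0.964 (pooled) or 0.960 (Welch), in line with the stated figure of around 95%.

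**3. Size of the consequence if the printed null is coded with c = control.**
- SD: 7 min / 0.5 = 14 min for the control sample. The same SD in the POCT group is an assumption.
- SE = 14 × √(1/50 + 1/900) = 2.034 min.
- Welch df = (1/50 + 1/900)² / [(1/50)²/49 + (1/900)²/899] = 54.6, so t(0.95) = 1.673.
- Printed null: reject if (x̄c − x̄t − 7)/2.034 < −1.673; noncentrality (−δ − 7)/2.034.
- Intended null: reject if (x̄t − x̄c − 7)/2.034 < −1.673; noncentrality (δ − 7)/2.034.

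Probability of declaring no impact:

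| True δ (min) | Printed null | Intended null |
|---|---|---|
| −7 | 5.0% | about 100% |
| −3.5 | 52% | 99.97% |
| 0 | 96.0% | 96.0% |
| 3.5 | 99.97% | 52% |
| 7 | about 100% | 5.0% |
| 14 | about 100% | about 0% |

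Simulation with 4,000 runs per scenario agrees: 0.956 (printed) and 0.960 (intended) at zero delay, 1.00 and 0.056 at 7 min.

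The two versions agree at δ = 0, which is where power is calculated. The sample-size figures are therefore the same for either direction and cannot show which one was meant.

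**The case against.** The strongest reply is that nobody reading the whole section would run the test backwards. The null in words, the non-inferiority label and the type I error sentence all point one way. With c as control, the printed HA is exactly the right alternative, so a test coded from HA behaves correctly. With the literal with/without order, the printed null itself is right. The failure in the table needs one labelling and one coding choice together. An independent statistical team does the analysis, and the outcome is secondary. The sentence that introduces the null in words leaves the direction open but is not wrong; the fault is in the formula after it. The calculation also ignores the restriction to babies given antibiotics within 2 hours of admission, which limits how far long delays could appear in the data.

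Most of this stands. It shows that the intent can be recovered and that a notation error is the likely explanation. It does not make the formula correct: under either labelling one hypothesis is reversed and the pair is not complementary.

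A reader might infer that the trial's test declares no impact however long the POCT delays antibiotics. The documents do not support that. It would follow only if the code were built on the printed null with c as control, and the article does not show that it was.

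**Conclusion.** The formula is misstated and should be corrected. With the subscripts as used for the sample sizes, the null has the wrong sign, the hypotheses overlap, and a delay of Δ or more lies in neither. The order in which the means are introduced adds a second, conflicting labelling. Because the prose and the printed HA give the intended direction, this is probably a notation error. The required sample of 112 and the stated power are unaffected.

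The conditional risk is a chance of about 100%, instead of 5%, of declaring no impact at a true delay of 7 min. It rests on three conditions: coding from the printed null, c meaning control, and an SD of about 14 min in both groups with samples of 50 and 900. The point warrants a correction and a code check. It does not support a claim that the analysis was run in the wrong direction or that the design is underpowered.

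**What to change.** Define the symbols once: μt is the mean time with the POCT and μc the mean time before implementation. Reorder the sentence that introduces the means to match, and drop the U notation. Then write

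H0: μt − μc ≥ Δ versus HA: μt − μc < Δ,

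with Δ the margin already set in the sample-size section (0.5 SD, about 7 min). Confirm that the one-sided Welch test is coded in this direction. A simple check is to add a large artificial delay to the POCT times and see that the null is then not rejected. Reporting the upper one-sided 95% Welch confidence limit for μt − μc against Δ would be an equivalent way to state the same rule, and is optional.

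The cost is one corrected line and a check of the code. No new data and no change to the sample size are needed. The article reports recruitment closed and analysis ongoing, so the check belongs with that analysis.

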### Study centres and time schedule

Participants will be recruited from two large UK based NICUs in the UK, Manchester University National Health Service (NHS) Foundation Trust and Liverpool Women’s NHS Foundation Trust (LWH). Both sites will recruit participants and conduct the trial. It should be noted that there is considerable variation in antimicrobial prescribing practices both between and within different countries. The type of antibiotics used, dosing regimens and monitoring protocols can vary between different nations, cities and institutions.^8^ Both units in this study use a combination of a beta-lactam and an aminoglycoside as first line therapy for early onset neonatal infection. Based on historical data, the majority of admissions to both units will be screened for infection and, as such, considered for antibiotic therapy. The trial began in January 2020 and the last participant was recruited in November 2020. The study continued despite the SARS-CoV-2 pandemic.

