### Inclusion criteria

All babies admitted to NICU across the two participating sites, commencing from the trial start date. This includes babies admitted directly from delivery suite, midwifery led units or transferred from another neonatal unit. At the LWH site, babies who are screened for infection on the NICU but then transferred to external wards (not formally admitted to NICU) will also be included. It is a clinical decision whether the babies are being screened for infection as part of their assessment, reflecting the real-world, pragmatic, nature of the trial. This also reflects the variation in admission procedures between the two trial sites where pathways differ due to local practices.

Given that all babies admitted to NICU are eligible for recruitment, some of those recruited will not go onto receive antibiotic therapy. If the baby did not go onto receive antibiotics, their data will still form part of the dataset for analysis.

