### Exclusion criteria

Babies requiring antibiotics immediately, as determined by the admitting clinician, with already established intravenous access. These exclusion criteria recognise the potential urgency of any decision to deliver antibiotics. If intravenous access has not been achieved, then this may provide time to run the assay. We expect that only a small proportion of admissions would be excluded based on these criteria.

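### The timing non-inferiority test is a crude before-after comparison pooled over two differing sites, so a change in site mix or calendar period would be read as an effect of the point of care test (POCT)

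*Protocol article*

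**What the plan says.** The Statistical analysis section sets out a non-inferiority question about time from admission to antibiotics, among babies treated within two hours of admission. It describes the contrast as with versus without the POCT and settles it by one procedure: "a one-sided Welch t-test will be used to reject or not reject the null hypothesis". The Welch form is justified by unequal group sizes and unknown, possibly unequal variances. No site, period or case-mix term is named.

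The two groups come from different calendar periods. Under Secondary outcomes: "A reference time to antibiotic was measured over a month-long period before implementation". The control group is put at about 50. Under Study centres and time schedule: "The trial began in January 2020 and the last participant was recruited in November 2020", followed by "The study continued despite the SARS-CoV-2 pandemic". The test group is forecast at about 900.

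The Inclusion criteria refer to "the variation in admission procedures between the two trial sites where pathways differ due to local practices". They also add, at one site only, babies screened on the unit but never formally admitted to it.

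The only time-related analyses described are by assay update: post hoc in the Statistical analysis section, and as per-update reporting in the Discussion. The limitation named at the front of the article is the rarity of the variant, not before-after confounding.

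**The concern.** A two-sample t-test estimates the POCT effect only if the two groups would have had the same mean time without the POCT. Two features of this design put that in doubt. First, if mean times differ between the sites and each site's share of the sample changes between periods, the pooled means differ even when the POCT does nothing. Second, anything else that changed between the baseline month and 2020 enters the difference in full. Enlarging the test sample removes neither.

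This is the only formal hypothesis test in the article. It also bears on the part of the primary objective about not disrupting standard care. A favourable shift could hide a real delay; an unfavourable one could make a harmless test look disruptive.

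**Working it through.** **Inputs from the article (Samples size; Statistical analysis).** Margin 0.5 in Cohen's d, about 7 min, so SD = 7 / 0.5 = 14 min. Control n = 50, forecast test n = 900, 5% significance level, one-sided test. The two printed hypotheses subtract the means in opposite orders. I take the direction from the article's description of the type I error: non-inferiority is declared when the test-minus-control difference is shown to be below 7 min.

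**The plan's own figures.** A pooled two-sample t calculation with 50 controls, d = 0.5 and one-sided 5% gives a test sample of 112 for 90% power, exactly as stated (Welch degrees of freedom give 115). With 900, power is 96.0% (Welch) to 96.4% (pooled t or normal approximation), against a stated figure of around 95%. The arithmetic is sound; the issue is bias.

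**Standard error.** SE = √(14²/50 + 14²/900) = √(3.920 + 0.218) = 2.03 min.

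**Effect of a non-POCT shift of b minutes (assumed; the article gives none).**
- Favourable shift, true POCT delay 7 min: type I error = Φ(b/2.034 − 1.645).
- Unfavourable shift, true POCT delay 0: power = Φ((7 − b)/2.034 − 1.645).

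| b (min) | Type I error, favourable | Power, unfavourable |
|---|---|---|
| 0 | 5% | 96% |
| 0.5 | Φ(−1.40) = 8% | Φ(1.55) = 94% |
| 1 | Φ(−1.15) = 12% | Φ(1.30) = 90% |
| 2 | Φ(−0.66) = 25% | Φ(0.81) = 79% |
| 3 | Φ(−0.17) = 43% | Φ(0.32) = 63% |

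Noncentral t with Welch degrees of freedom agrees: 12% and 25% for type I error, 90% and 78% for power, at 1 and 2 min.

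**A smaller test group.** The 900 is based on the "expected number of admissions across both clinical sites over an approximate 10-month trial period", so fewer babies will enter the two-hour timing comparison. With a test group of 112, a 2-min shift gives a type I error of 21%, or power of 67% instead of 90%. The problem does not depend on the 900.

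**How a shift could arise from site mix.** b = change in site share × difference between site means. If the mix is the same in both periods, b = 0 however much the sites differ. Assumed examples: a 10-point change with a 5-min gap gives 0.5 min; 20 points with 10 min gives 2 min; 20 points with 15 min gives 3 min.

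**How a shift could arise from calendar time.** If monthly means varied with an SD of 2 min (assumed), SE = √(3.920 + 2² + 0.218 + 2²/10) = √8.538 = 2.92 min, and the nominal 5% test would have a type I error of Φ(−1.645 × 2.034/2.92) ≈ 13%. The single control month carries its monthly deviation undiminished.

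**The case against.** The strongest reply is that every bias figure is assumed. The article gives no site means, no site split for the control month and no pandemic effect. Some of the illustrative gaps are large against an SD of 14 min: at a 50:50 mix, a 15-min site gap would account for 7.5²/14² = 56/196, about 29%, of the variance. This stands. A reader might infer that the test's error rate is definitely not 5%. The documents show only that nothing in the analysis protects it.

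A reader might also set about 50 controls in a month against 900/10 = 90 a month and infer different selection. That does not follow. The 900 is based on expected admissions, and the Inclusion criteria say some recruited babies receive no antibiotics, whereas the controls are a time-to-antibiotic sample. The two figures are compatible with identical selection.

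Nor do the documents show that the exclusion ("Babies requiring antibiotics immediately, as determined by the admitting clinician, with already established intravenous access") applied to one period only. The article is silent on eligibility in the control month and expects few exclusions. If those babies are the fastest treated and were dropped only from the test period, the test-period mean would rise, which works against declaring non-inferiority.

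Finally, site tables and sensitivity analyses often belong in a statistical analysis plan, and reporting by assay update gives a partial, conditional look at calendar time. But the article itself fixes the samples, the test and the decision rule, and attributes the contrast to the POCT. This is therefore a stated choice, not an omitted detail, and reporting by update adjusts for neither site nor the baseline month.

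**Conclusion.** The point holds as a structural weakness of a secondary outcome. The decision rests on a crude difference between one pre-implementation month and about ten months of 2020, pooled over two sites with differing pathways, and the Welch correction does not address that. The size and direction of any bias are unknown. With an SD of 14 min, a 7-min margin and groups of 50 and 900, assumed shifts of 1 to 3 min, well inside the margin, would move the type I error from 5% to about 12–43% or power from 96% to about 90–63%.

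It would be tempting to conclude that an adjusted model recovers the POCT effect. It does not: with one baseline month, period and POCT are aliased, so site mix can be adjusted for but pandemic and seasonal effects cannot be separated. The primary outcome is descriptive and unaffected. The change should be made, but it does not undermine the study as a whole.

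**What to change.** - Replace the crude Welch test with a linear model for time to antibiotic with terms for period and site, plus demographics if available in both periods. Use heteroscedasticity-robust (HC3) standard errors, which keep the allowance for unequal variances. Declare non-inferiority if the one-sided 95% upper limit for the period difference (test minus control) is below the same 7-min margin.
- Apply the same eligibility rules to both periods, including the exclusion criterion and the one-site extension, and state that this was done.
- Report the before-after difference for each site.
- Word the result as a before-after difference, not as the effect of the POCT, and list the single baseline month and the pandemic as limitations.
- Add a comparison limited to pre-pandemic POCT months as a sensitivity analysis only. It is less precise and is confounded with early learning and assay updates.

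The cost is slightly more analysis work, changed wording and a few more tables, with no new recruitment. The article's list of recorded variables does not name site, but site is known from the recruiting centre. Whether demographics exist for the control month must be checked. The Trial status section says analysis was still under way, so the change was feasible.
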